### **Red blood cell metabolism analysis**

In the subgroup of patients with cytopenia and bone marrow dysplasia, enzymatic activity of glycolytic enzymes will be studied on an aliquot of the blood sample collected at enrollment, and activity of some glycolysis-activating drugs may be measured in vitro. No genetic studies will be performed. The aliquot will be taken from the main study blood sample and used to determine the activity of red blood cell glycolytic chain enzymes. Glycolytic activity will be measured at baseline and after 6-hour in vitro incubation with AG946.

[figure not shown][figure not shown]

Dipartimento di Medicina Interna  
UOC EMATOLOGIA  
Pad. Marcora / Granelli  
Direzione [contact]  
Amb: [name] - DH: [name]  
Reparti: CTMO [name] - AOE [name]  
Mail: [contact]

- Direttore: [name]

### Statistical analysis

Since the study has a purely descriptive purpose, aimed at understanding the distribution and parameters of the variable under study (number of diagnostic tests per patient), and no data are available in the literature on this matter, the sample size is estimated based on the number of newly diagnosed autoimmune cytopenia patients expected to be diagnosed in one year at the proposing UOC (100 new cases/year; 200 total new cases considering the 2-year enrollment period), autoimmune cytopenia being a rare disease with estimated prevalence of 1-3 new cases per  $10^5$  (Barcellini et al., Blood 2014).

The diagnostic utility of performed tests will be evaluated by calculating their sensitivity and specificity, with particular reference to the definitive hematologic diagnosis in patients hospitalized in a ward.

The cytokine profile and microbiota identified at diagnosis and at follow-up points or relapses will be correlated with clinical outcomes, measured in terms of response to specific therapy, relapse-free survival (RFS), defined as the time interval between response to a given therapy and relapse, and the occurrence of main complications (thrombosis, acute renal failure, and infections). RFS curves will be constructed using the Kaplan-Meier method and compared by the Log-rank test or Cox proportional hazards model.

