## 2. STUDY OBJECTIVES

### 2.1 Primary Objective

- Characterize the diagnostic pathway of newly diagnosed autoimmune cytopenia patients hospitalized or attending the Hematology outpatient clinics of this hospital.

[figure not shown][figure not shown]

Dipartimento di Medicina Interna  
UOC EMATOLOGIA  
Pad. Marcora / Granelli  
Direzione [contact]  
Amb: [name] - DH: [name]  
Reparti: CTMO [name] - AOE [name]  
Mail: [contact]

- Direttore: [name]

- Determine sensitivity and specificity of the tests used and prepare a list of recommended diagnostic tests for autoimmune cytopenia at various clinical levels.

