## 3. STUDY DESIGN

### 3.1 Design

The study will enroll patients with anemia ( $Hb < 12 \text{ g/dL}$ ), thrombocytopenia (platelets  $< 100,000/\text{mm}^3$ ), and neutropenia (neutrophils  $< 1000/\text{mm}^3$ ) without prior hematologic diagnosis, hospitalized or attending Hematology outpatient clinics. Diagnosis of autoimmune cytopenia will follow current accepted criteria for AIHA (evidence of hemolysis and positive/negative direct Coombs test after exclusion of other hemolysis causes), ITP (exclusion of other thrombocytopenia causes, with or without anti-platelet antibodies), and CIN (exclusion of other neutropenia causes, with or without anti-neutrophil antibodies).

To ensure informative clinical follow-up on test sensitivity and specificity and to establish a control group, all newly diagnosed cytopenia patients without known primary cause will be enrolled. Patients will be classified by severity and, for AIHA, by antibody characteristics:

- Moderate ITP: platelets  $> 30,000/\text{mm}^3$
- Severe ITP: platelets  $< 30,000/\text{mm}^3$
- Mild neutropenia: neutrophils  $> 1000/\text{mm}^3$
- Moderate neutropenia: neutrophils  $500\text{--}1000/\text{mm}^3$
- Severe neutropenia: neutrophils  $< 500/\text{mm}^3$
- Warm AIHA: monospecific direct Coombs positive for IgG or IgG+C low titer, no autoagglutination at  $20^\circ\text{C}$
- Cold AIHA: monospecific direct Coombs positive for C3d fraction and/or cold agglutinins with or without autoagglutination at  $20^\circ\text{C}$

[figure not shown][figure not shown]

Dipartimento di Medicina Interna  
UOC EMATOLOGIA  
Pad. Marcora / Granelli  
Direzione [contact]  
Amb: [name] - DH: [name]  
Reparti: CTMO [name] - AOE [name]  
Mail: [contact]

- Direttore: [name]

- Mixed AIHA: monospecific direct Coombs positive for high-titer IgG+C and autoagglutination at 20°C and/or dual specificity for anti-Rh and anti-I/i/IH
- Atypical AIHA: monospecific direct Coombs positive for IgA, for warm IgM, or direct Coombs negative after exclusion of other hemolysis causes.

Availability of clinical information at diagnosis and follow-up updates for at least 3 years are key inclusion criteria.

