## 4. STUDY PROCEDURES

### 4.1 Intervention

Enrollment:

- Venous blood draw for somatic DNA mutation and cytokine profile studies
- Nasopharyngeal swab and fecal sample for microbiota analysis
- Medical history, physical exam, anthropometrics
- Blood, urine, and instrumental tests as clinically indicated to assess hematologic disease status
- For the marrow substudy, samples will be used to study immunological microenvironment, cytokine patterns, and RBC metabolism.

Follow-up (every 1–3 months for AIHA and ITP, every 6–12 months for CIN, according to clinical need):

- Blood for cytokine profiling
- Nasopharyngeal swab and fecal sample for microbiota analysis

[figure not shown][figure not shown]

Dipartimento di Medicina Interna  
UOC EMATOLOGIA  
Pad. Marcora / Granelli  
Direzione [contact]  
Amb: [name] - DH: [name]  
Reparti: CTMO [name] - AOE [name]  
Mail: [contact]

- Direttore: [name]

- Medical history, physical exam, anthropometrics
- Blood, urine, instrumental tests as indicated

At relapse:

- Blood/marrow, nasopharyngeal swab, fecal sample, clinical evaluation, and lab tests as above. Samples stored at the Hematology and Transfusion Medicine Laboratory biobank.

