## 5. ENDPOINT

### 5.1 Primary endpoint

Number of laboratory tests required to reach the diagnosis of autoimmune cytopenia for each patient.

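### Sensitivity and specificity, part of the primary objective, are set against a diagnosis that some of the tests define, use only patients whose clinician ordered the test, and have no endpoint

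*Protocol*

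**What the plan says.** The second bullet of section 2.1 (Primary Objective) reads: "Determine sensitivity and specificity of the tests used and prepare a list of recommended diagnostic tests for autoimmune cytopenia at various clinical levels".

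The Statistical analysis text, an unnumbered heading within section 7, gives the method in one sentence. "The diagnostic utility of performed tests will be evaluated" and this is done "by calculating their sensitivity and specificity, with particular reference to the definitive hematologic diagnosis in patients hospitalized in a ward".

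Section 3.1 says how the diagnosis is made. For AIHA it is "evidence of hemolysis and positive/negative direct Coombs test after exclusion of other hemolysis causes". ITP and CIN are diagnoses of exclusion, and the respective antibodies may be present or absent. The same section uses the Coombs pattern to separate warm, cold, mixed and atypical AIHA. It also enrols all new cytopenias without a known primary cause, partly to supply a control group, and asks for at least 3 years of follow-up.

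Section 4.1 says who gets which test: "Blood, urine, and instrumental tests as clinically indicated to assess hematologic disease status". Section 1.1 acknowledges that the test list is not standardized.

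The only primary endpoint, in section 5.1, is "Number of laboratory tests required to reach the diagnosis of autoimmune cytopenia for each patient". Section 5.2 adds the type of laboratory tests and the number and type of imaging tests.

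**The concern.** An accuracy figure is informative when the reference diagnosis is reached separately from the test being judged, and when the patients tested represent those in whom the test would be used. The protocol secures neither.

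Where a test is a required part of the definition, its result in cases is settled before any data are collected. Where a test is optional but known to the diagnosing clinician, it can pull the diagnosis towards agreement. Where a test is ordered selectively, the tested cases and controls may differ from the untested ones in ways that are linked to the result.

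The product at stake is the recommended test list. On this plan, part of it would rest on built-in figures and part on figures from whoever happened to be tested, so it could reproduce present ordering habits. The one primary endpoint, a count of tests, cannot yield sensitivity or specificity, so this half of the primary objective has no endpoint.

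**Working it through.** **The plan's own figure.** Section 7.1 expects 40 AIHA, 40 ITP and 20 CIN patients a year. (40 + 40 + 20) × 2 years = 200, which reproduces the stated sample size. AIHA alone gives 40 × 2 = 80. The protocol gives no number of controls, no expected sensitivity or specificity, and no ordering rates. Apart from the 80 AIHA cases, every input in steps 2 and 3 is therefore an assumption.

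**Step 1: what is fixed by definition (no assumption needed).** The section 3.1 definitions sort the tests as follows.

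| Test group | Role in section 3.1 | Consequence |
|---|---|---|
| Hemolysis criterion, as a set | Required for AIHA | Sensitivity for AIHA = 100% by construction; specificity not fixed |
| Tests that exclude other causes | Must not establish another cause (AIHA, ITP, CIN) | Negative in cases by construction |
| Direct Coombs | Either result allowed; pattern defines AIHA subtype | Sensitivity for AIHA not fixed; accuracy for subtype built in |
| Anti-platelet, anti-neutrophil antibodies | Either result allowed | Sensitivity not fixed |

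**Step 2: a test that is known but not required.** Take 80 AIHA cases, 80 controls, true sensitivity 0.80 and true specificity 0.90. Then TP = 64, FN = 16, TN = 72, FP = 8. Let a share w of discordant patients be classified to agree with the test:

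- apparent sensitivity = (TP + w·FP) / (TP + w·FP + (1 − w)·FN)
- apparent specificity = (TN + w·FN) / (TN + w·FN + (1 − w)·FP)

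Results:

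- w = 0.25: 66/78 = 0.846 and 76/82 = 0.927
- w = 0.50: 68/76 = 0.895 and 80/84 = 0.952
- w = 1: 1.00 and 1.00

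With 40 to 160 controls, w = 0.50 gives sensitivity 0.892 to 0.900 and specificity 0.957 to 0.950. Because section 3.1 accepts Coombs-negative AIHA, w = 1 is not what the protocol describes for that test. The actual w is unknown.

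**Step 3: selective ordering.** Assume half the patients are typical (sensitivity 0.90, specificity 0.85) and half mild (0.60, 0.95). With ordering rates a (typical) and b (mild):

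- observed sensitivity = (0.90a + 0.60b)/(a + b)
- observed specificity = (0.85a + 0.95b)/(a + b)

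| a, b | Sensitivity | Specificity |
|---|---|---|
| Everyone tested | 0.750 | 0.900 |
| 0.9, 0.6 | 0.780 | 0.890 |
| 0.9, 0.3 | 0.825 | 0.875 |
| 0.9, 0.1 | 0.870 | 0.860 |
| 0.3, 0.9 (reversed) | (0.27 + 0.54)/1.2 = 0.675 | (0.255 + 0.855)/1.2 = 0.925 |

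A second set of assumptions lets cases and controls have their own mix.

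- Controls: 30% resemble cases (specificity 0.70, 80% tested) and 70% do not (0.95, 15% tested). True specificity is 0.3 × 0.70 + 0.7 × 0.95 = 0.875. Observed specificity is (0.3 × 0.8 × 0.70 + 0.7 × 0.15 × 0.95)/(0.3 × 0.8 + 0.7 × 0.15) = 0.26775/0.345 = 0.776.
- Cases: half typical (sensitivity 0.90, 90% tested) and half atypical (0.70, 40% tested). True sensitivity is 0.80. Observed sensitivity is (0.405 + 0.140)/0.65 = 0.838.

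If ordering is unrelated to the test result within disease status, this bias is zero. The reversed row shows that its sign also depends on who is tested.

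**Step 4: endpoints.** Sections 5.1 and 5.2 cover the number of laboratory tests, their type, and the number and type of imaging tests. None is an accuracy measure.

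**The case against.** The strongest reply is that section 3.1 is built to avoid circularity. It accepts either Coombs result and does not require platelet or neutrophil antibodies, so a negative result does not bar the diagnosis. This stands. A reader might infer that the accuracy of every autoimmune test is fixed by definition, and the protocol does not support that. Nor does it require any single hemolysis index, so one index taken alone need not be 100% sensitive; only the criterion as a set is. What remains is that the antibody results are available to those who make the diagnosis.

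A second reply is that the control group and the follow-up of at least 3 years were included with sensitivity and specificity in mind. They help, but the protocol does not say that the definitive diagnosis draws on follow-up or is reached apart from the test under study.

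Third, a reader might take the emphasis on ward patients to mean that outpatients are dropped. The wording gives inpatients particular attention without excluding others, and sections 1.1 and Expected results share that emphasis.

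Fourth, the size of the selective-testing bias cannot be derived from the documents. This is correct, and the figures above are illustrations only.

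Finally, a statistical analysis plan may exist and hold the tabulations. It could, but the reference diagnosis, the set of tests counted and the endpoints for a primary objective are stated in the protocol itself.

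**Conclusion.** The point holds in a limited form. Two consequences follow from section 3.1 without any assumption: the hemolysis criterion as a set is 100% sensitive for AIHA, and exclusion tests are negative in cases. Reported as accuracy, these figures would carry no information. For the Coombs and antibody tests the circularity is weaker and of unknown size, except that Coombs accuracy for AIHA subtypes is built in. For all tests ordered at discretion, the estimates describe a selected subset. They are biased if ordering depends on features linked to the result within disease status, which is plausible under clinician-led testing but not shown. It is also plain from sections 2.1, 5.1 and 5.2 that half of the primary objective has no endpoint.

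This should be fixed, but it does not undermine the study as a whole. The protocol calls its purpose descriptive, tests no hypothesis on accuracy, and already collects the follow-up that most of the remedy needs.

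**What to change.** In the Statistical analysis text:

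1. State that the reference diagnosis is the one held at the last available follow-up, using the 3-year follow-up already planned. This reduces misclassification but does not make the reference independent of the tests.
2. Report the hemolysis criterion and the exclusion tests that the section 3.1 definitions require as frequency and diagnostic yield, not as sensitivity and specificity for that diagnosis. Keep sensitivity and specificity for the Coombs, anti-platelet and anti-neutrophil tests, and state that the result was available to those making the diagnosis. Removing every test named in section 3.1 would go too far, because it would strip the main autoantibody tests from the objective.
3. For each test, give the numbers tested and untested by final diagnosis and by inpatient or outpatient setting. Base the recommended list on estimates read with those counts. An estimate weighted for the probability of being tested is optional, as a sensitivity analysis. It corrects only for recorded drivers of ordering and may be unstable with about 20 × 2 = 40 CIN cases.

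In section 5:

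4. Add per-test sensitivity and specificity as the endpoint for the second primary objective, and describe the existing count as tests performed up to diagnosis.

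The cost is protocol wording and some extra tabulation of data already collected. The downside is that fewer tests receive an accuracy figure.

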## 2.2 Secondary Objectives

- Evaluate clinical and laboratory markers predictive of therapeutic response and complications, particularly infections, through longitudinal collection of clinical data, serum/plasma/bone marrow samples, nasopharyngeal swabs, and fecal samples during the observational study period.
- Preliminary correlation analysis between identified somatic DNA mutations, cytokine patterns, microbiota complexity at diagnosis and during disease course with therapeutic response, relapses, and complications (especially infections).
- Evaluate red blood cell metabolism in a subgroup of patients with cytopenias and bone marrow dysplasia and measure in vitro activity of glycolysis-activating drugs (specific substudy objective).

---

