## 7. EXPERIMENTAL DESIGN

### 7.1 Sample size

On average, our Center annually evaluates 40 new patients with autoimmune hemolytic anemia (AIHA), 40 with immune thrombocytopenia (ITP), and 20 with cytopenia of undetermined significance (CIN). Therefore, enrollment of at least 200 patients is expected. Considering that the relapse risk is approximately 30% in AIHA and ITP and most relapses occur within the first 24 months from onset, it is reasonable to estimate that about 40-50 patients will experience relapse during the three-year follow-up.

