### **Microbiota analysis**

For each enrolled case, a nasopharyngeal swab and a fecal sample will be collected at enrollment and at any relapse, prior to the administration of any new line of therapy. Respiratory/fecal samples collected will undergo bacterial genomic DNA extraction and amplification of the hypervariable V1–V3 region of the 16S rRNA gene. Library preparation and subsequent sequencing using the MiSeq Illumina method will enable precise characterization of the resident flora, at least at the bacterial genus level. Data will be analyzed with appropriate statistical methods to evaluate potential differences in nasal/fecal microbiota composition during follow-up and in relation to different therapies administered.

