#### **10.2.3 Informed Consent (IC)**

The investigator or designated personnel must inform subjects about all aspects and procedures of the study.

The informed consent process must comply with applicable regulatory procedures. The investigator (or designated collaborator) and the subject must date and sign the consent form before any study-related procedures. Subjects receive a copy of the signed IC; the original is kept in designated study archives. Neither investigator nor staff may coerce or unduly influence subjects to participate or continue in the study. Participation must be voluntary, and subjects must be informed they may withdraw consent at any time without penalty or loss of benefits.

Written or oral study information, including consent forms, must not contain language that waives

[figure not shown][figure not shown]

Dipartimento di Medicina Interna  
UOC EMATOLOGIA  
Pad. Marcora / Granelli  
Direzione [contact]  
Amb: [name] - DH: [name]  
Reparti: CTMO [name] - AOE [name]  
Mail: [contact]

- Direttore: [name]

subjects' legal rights or releases investigators or sponsors from liability for negligence.

Patients meeting inclusion criteria will be invited to provide peripheral blood samples for cytokine profiling during scheduled visits and symptom-driven visits, and consent to use of their personal and clinical data for research. Nasopharyngeal swabs and fecal samples will be collected at enrollment and at 1, 3, 6, and 12 months for microbiota complexity studies.

Patients will have adequate time to read the information and ask questions.

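### The RFS analysis does not limit which biomarker sample may explain which relapse-free interval, so it allows immortal-time bias and reverse causation

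*Protocol*

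**What the plan says.** The Statistical analysis text of the Protocol names the sampling times: "The cytokine profile and microbiota identified at diagnosis and at follow-up points or relapses will be correlated with clinical outcomes". The outcomes are response to therapy, RFS, and main complications. RFS is "defined as the time interval between response to a given therapy and relapse". The method follows: "RFS curves will be constructed using the Kaplan-Meier method and compared by the Log-rank test or Cox proportional hazards model".

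Section 2.2 has the same scope, relating "microbiota complexity at diagnosis and during disease course with therapeutic response, relapses, and complications".

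The sampling times are described in three ways:
- Section 4.1 sets follow-up sampling "every 1–3 months for AIHA and ITP, every 6–12 months for CIN, according to clinical need".
- The Microbiota analysis text, which places relapse samples before the next treatment line, says "a nasopharyngeal swab and a fecal sample will be collected at enrollment and at any relapse, prior to the administration of any new line of".
- Section 10.2.3 says "Nasopharyngeal swabs and fecal samples will be collected at enrollment and at 1, 3, 6, and 12 months for microbiota complexity studies".

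The Protocol mentions no landmark time and no time-dependent covariate. It has no rule linking a sample to an RFS interval.

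**The concern.** Kaplan-Meier curves compared by log-rank need groups that are known when the clock starts. A follow-up sample taken after response does not meet this condition. A patient has to remain relapse-free to reach the later visits, so a longer RFS gives more chances to be classed as having a given profile. A marker with no prognostic value can then look protective.

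A sample taken at relapse raises a different problem. If it is used to explain the interval that has just ended, the marker may be a consequence of the relapse and not a predictor of it.

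The Expected results section calls it a major goal to learn whether these profiles can be used to infer response, relapse risk and complications, and section 1.1 looks ahead to dynamic markers that anticipate relapse. Follow-up samples are therefore meant to be used in this way. The sentence that names sampling times, outcome and method together is the place to settle how.

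**Working it through.** **1. The plan's own figures.** Section 7.1: "On average, our Center annually evaluates 40 new patients with autoimmune hemolytic anemia (AIHA), 40 with immune thrombocytopenia (ITP), and 20" with CIN. Section 6 gives two years of enrolment.
- Patients: (40 + 40 + 20) × 2 = 200, as stated.
- AIHA and ITP patients: (40 + 40) × 2 = 160.
- Relapses at the stated 30% risk: 0.30 × 160 = 48, inside the stated 40-50.

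The Protocol gives no significance level, power or effect size for RFS, so no power check applies.

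**2. The mechanism by hand.** Assume (not from the Protocol) that each sample is high with probability 0.2, independently, and that a patient is classed *ever high* if any sample so far was high. The chance after k samples is 1 − 0.8^k.
- Sampling at diagnosis and months 1, 3, 6, 12. Relapse at month 2: k = 2, 1 − 0.64 = 0.36. Relapse-free beyond month 12: k = 5, 1 − 0.328 = 0.67.
- Sampling at diagnosis and every 3 months (months 3 to 33). Relapse at month 2: k = 1, 0.20. Relapse-free to month 36: k = 12, 1 − 0.069 = 0.93.

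The marker has no effect, yet early relapsers fall mostly into the never-high group.

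**3. Size under the null.** Taken from the Protocol: 160 AIHA/ITP patients, 30% relapse by 36 months, and visits at 1, 3, 6, 12 months (section 10.2.3) or every 3 months (the sparse end of section 4.1 for AIHA and ITP). Assumed: the clock starts at enrolment, marker values are independent of relapse and of each other, the test is a two-sided 5% log-rank, and the grouping is *ever high*. Two relapse timings were used:
- A: 80% of relapses uniform over months 0-24, the rest over months 24-36.
- B: Weibull with shape 0.8.

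Share of null studies rejected (400-1000 runs per scenario):

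| Timing, samples used | High per sample | 1/3/6/12 months | 3-monthly |
|---|---|---|---|
| A, diagnosis + follow-up | 10% | 10.2% | 96.5% |
| A, diagnosis + follow-up | 20% | 17.3% | 99.8% |
| A, diagnosis + follow-up | 30% | 27.3% | 100% |
| A, follow-up only | 20-40% | 25-52% | not tabulated |
| B, diagnosis + follow-up | 20-40% | 25-56% | 100% |
| B, follow-up only | 20-40% | 35-75% | not tabulated |
| A, diagnosis only | 10-30% | 4-6% | about 6% |
| A, 6-month landmark | 10-30% | about 4-5% | about 5% |

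With 600 runs, simulation error around 5% is ±1.96 × √(0.05 × 0.95 / 600) = ±1.7 points, so the last two rows agree with the nominal level. Under A with the 1/3/6/12 schedule, the spurious hazard ratio for diagnosis plus follow-up is about 0.82, 0.72 and 0.59 at 10%, 20% and 30% high.

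**4. Counting the relapse sample as well.** Suppose, under timing A, that 40% of relapse samples are high purely as a consequence of relapse. As the chance of a high value per sample goes from 10% to 20% to 30%, rejection is 64.5%, 15.5% and 5.3% with the 1/3/6/12 schedule (apparent hazard ratios 2.0, 1.37, 1.08). With 3-monthly sampling it is 17.7%, 83.3% and 96.5%, in the protective direction. The two biases oppose each other and can partly cancel.

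**5. Cost of a landmark.** Under timing A, relapses before month 6 are 48 × 0.8 × 6/24 = 9.6. About 10 of 48 are lost and about 38 remain.

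**The case against.** A reader might infer that the plan builds the bias in, so that a useless marker will come out as prognostic. The text does not go that far:
- It includes diagnosis samples, for which Kaplan-Meier with log-rank is valid.
- It offers Cox as an alternative, and Cox can take time-dependent covariates.
- It lists several outcomes without assigning every sampling time to RFS.
- It states no grouping rule. *Ever high* is an assumption, and a marker that is stable within a patient would show much less of this bias.

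A reader might also infer that a relapse sample can never be a predictor. That is not supported either. RFS is defined per given therapy, and relapse swabs and fecal samples precede the next line, so such a sample is a legitimate baseline for response and RFS on that next line.

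Two further inferences are not demonstrated. One is that visits by clinical need distort the results: section 4.1 bounds the intervals, section 10.2.3 gives fixed times, and the simulation does not model informative sampling. The other is that steroid effects enter the enrolment cytokine profile: no text places that draw after treatment.

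Finally, the choice of sample and landmark could be left to a statistical analysis plan, and the biomarker work is secondary, preliminary and described as a pilot. All of this lowers the severity. It does not remove the point, because the Protocol itself combines post-response samples, RFS and log-rank in one paragraph, and an analysis that followed it literally could be invalid.

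**Conclusion.** The point holds as a gap that permits bias, not as a certain error. Nothing in the Protocol stops groups being formed from samples taken after response, or a relapse sample from being tied to the interval it ends.

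If *ever high* grouping were used, false rejection would be about 10-75% with the 1/3/6/12-month schedule and about 96-100% with 3-monthly sampling to month 36, against about 4-6% with diagnosis-only or landmark grouping. These figures rest on the assumed grouping rule, a 10-40% chance of a high value per sample, independence within patient, the two relapse timings, and a clock that starts at enrolment. Counting relapse samples can pull the other way.

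Severity is moderate. The primary endpoint (number of laboratory tests, section 5.1), the sample size and the sample collection are unaffected.

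**What to change.** Add to the Statistical analysis text:

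1. Kaplan-Meier with log-rank is used only for groups defined by samples taken at or before the start of the RFS interval: the diagnosis sample for first-line RFS, and, where available, a relapse sample taken before the next line as baseline for RFS on that line.
2. Follow-up samples are analysed at a prespecified landmark among patients still relapse-free, with RFS counted from the landmark, or as time-dependent covariates in the Cox model using the last value before each event time.
3. A relapse sample is never a predictor of that same relapse. For the interval just ended, it is reported descriptively or as a paired comparison with the enrolment sample.

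The sampling times in section 4.1, the Microbiota analysis text and section 10.2.3 should also be reconciled, since the size of the bias and the choice of landmark depend on them.

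The cost is wording and some extra analysis, with no new samples. The drawback is that a landmark discards earlier relapses: about 10 of 48 at 6 months under timing A. The 6-month landmark is only an illustration; time-dependent Cox avoids this loss.
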